#### Potential effect modifiers

To examine which patient characteristics modify effectiveness of the intervention as reflected by increased physical activity level, pre-specified patient characteristics are selected, including age, BMI, level of education, social support, depression, patient-provider relationship and baseline number of minutes of physical activity. To identify potential effect modification, we will use GEEs for each of these patient characteristics separately. The independent variables in the models will be the patient characteristic, random intercept, interaction term for study arm and patient level. Effect modification will be considered significant if the interaction term shows a level of significance <0.05. All quantitative analyses will be performed using IBM SPSS Statistics for Windows version 21.0 software (IBM, Armonk, NY, USA).

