#### Sample size calculation

The present trial is powered to detect a mean difference between the intervention arm and control arm of 20% in number of minutes of at least a moderate level of physical activity. Based on the results of the It’s LiFe! trial [61], the mean level of physical activity in participants is 38 minutes (SD 18.1). The It’s LiFe! trial is a three-arm trial performed in primary care in the Netherlands with patients with chronic obstructive pulmonary disease and DM2 in which the researchers aimed to increase physical activity with a self-management support programme and the It’s LiFe! tool (a monitoring and feedback tool). This study revealed an increase in physical activity of 27%, but only in the counselling and It’s LiFe! tool group, objectively measured with the Pam AM300. We consider an increase in physical activity of 20% as reasonable to achieve. Taking a power of 80% and a significance level of 5% into account requires 89 patients per arm. Assuming an intra-cluster correlation of 0.05 and a cluster size of 8 patients per general practice requires 30 or 31 participating practices [59]. Allowing a patient dropout rate of 15%, we aim to recruit 279 patients in total and 9 or 10 patients per general practice.

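### The effect-modifier model lists an arm interaction but no study-arm main effect, and puts a random intercept in a GEE; fitted literally with uncentred characteristics, its test picks up the overall treatment effect

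*Protocol article*

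**What the plan says.** The Protocol article, section Potential effect modifiers, names seven pre-specified characteristics, "including age, BMI, level of education, social support, depression, patient-provider relationship and baseline number of minutes of physical activity". The method is given as: "To identify potential effect modification, we will use GEEs for each of these patient characteristics separately". The content of each model is then stated: "The independent variables in the models will be the patient characteristic, random intercept, interaction term for study arm and patient level". The decision rule is: "Effect modification will be considered significant if the interaction term shows a level of significance <0.05".

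The preceding section, Effectiveness of the activate intervention, assigns linear mixed models to continuous outcomes and GEE with a log link to binomial outcomes, and attaches random intercepts to the mixed models. The outcome here, minutes of moderate to vigorous activity, is continuous. No section adds a study-arm main effect to the effect-modifier models or says how the characteristics are coded or centred.

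**The concern.** Two things in the model sentence do not work.

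- **No arm main effect.** A product term tests modification only if both of its components are also in the model. Without the arm term, the two arms are forced to share one fitted value where the characteristic equals zero. For age, BMI or a questionnaire score, zero lies outside or at the edge of the data. The only way the model can represent a constant difference between arms is then through the product, so a constant benefit looks like a benefit that grows with the characteristic.
- **A random intercept in a GEE.** GEE is a marginal method that handles clustering through a working correlation and a robust variance. It contains no random effects, so the sentence cannot be carried out as written and the analyst has to guess which half was meant.

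Identifying which patient characteristics modify the change in activity is one of the stated secondary objectives and returns in the abstract and discussion. The first fault does most harm when the intervention works, which is when subgroup claims would guide implementation.

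**Working it through.** **Inputs from the Protocol article.** Sample size calculation: mean 38 minutes, SD 18.1, a 20% difference, 80% power, 5% significance; and "Assuming an intra-cluster correlation of 0.05 and a cluster size of 8 patients per general practice requires 30 or 31 participating practices". Potential effect modifiers: seven characteristics, each tested at 0.05.

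**Inputs assumed, because the article gives none (mean, SD).** Age 62, 8 (the eligibility range is 40–75); BMI 29, 4.5; social support 65, 14; depression 4.5, 3.5; patient-provider relationship 4.2, 0.7; three education levels; baseline minutes with the planning mean and SD and a correlation of 0.5 with the outcome.

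**Step 1: the plan's own figures.** The effect is 0.20 × 38 = 7.6 minutes. Per arm, n = 2 × (1.960 + 0.842)² × 18.1² / 7.6² ≈ 89.0, which agrees with the stated 89 (90 with the t distribution). The design effect is 1 + (8 − 1) × 0.05 = 1.35. Then 2 × 89 × 1.35 = 240.3 patients, and 240.3 / 8 = 30.0 practices, against the stated 30 or 31. The inputs are therefore safe to reuse.

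**Step 2: what the product estimates without an arm term.** Suppose every patient gains δ, so there is no modification. Let the characteristic X have mean m and SD s in both of two equal arms. Fitting Y = b0 + b1·X + b2·(arm × X) by least squares gives, in expectation,

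b2 = δ·m / (m² + s²).

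This is zero only if δ = 0 or m = 0. At the average patient the product stands for b2·m = δ·m² / (m² + s²).

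- Age: b2 = 7.6 × 62 / (3844 + 64) = 0.121 minutes per year. At age 62 this is 7.5 minutes, or 98% of the overall effect (3844 / 3908).
- Depression: b2 = 7.6 × 4.5 / (20.25 + 12.25) = 1.05 minutes per point. At the mean score this is 4.7 minutes, or 62% (20.25 / 32.5).
- Any centred characteristic: m = 0, so b2 = 0.

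**Step 3: how often the test would reject.** Simulated trials had 31 practices of 8 patients, SD 18.1, ICC 0.05, the same effect in every patient and no modification. The linear model used practice-clustered robust standard errors (GEE with independence working correlation), and the product was tested at 0.05.

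| Characteristic | As listed, 7.6 min | As listed, 3.8 min | Arm term added, 7.6 min |
|---|---|---|---|
| Age | 80% | 29% | 6% |
| BMI | 79% | 27% | 7% |
| Social support | 77% | 29% | 5% |
| Depression | 65% | 23% | 5% |
| Patient-provider relationship | 79% | 30% | 5% |
| Baseline minutes | 84% | 30% | 6% |
| Education (numeric / factor) | 75% / 66% | 27% / 23% | 5% / 6% |

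As listed but with no arm effect, the rates were 5–7%. Without an arm term but with the continuous characteristic centred, they were 4–6% at 7.6 minutes. A separate run with the same planning inputs gave 73–82% at 7.6 minutes and 27–35% at 3.8 minutes for uncentred age-, BMI- and depression-like variables, and about 6–8% with no effect, with centring or with the arm term restored.

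**Step 4: all seven tests together (3,000 simulated trials per setting).** As listed, an average of 5.5 of 7 characteristics were flagged at 7.6 minutes and 2.1 of 7 at 3.8 minutes. With the arm term, about 0.4 of 7 were flagged at either effect.

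**The case against.** The best defence is that this is shorthand. The sentence is loose throughout: it calls a random intercept an independent variable and speaks of patient level where the characteristic must be meant. Reading the product as arm by characteristic is itself an inference, though the natural one. The main analysis likewise mentions a time-by-arm interaction without listing main effects, and nobody would conclude that they are left out. The article also condenses a fuller protocol, and an experienced analyst would probably include the arm term.

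That defence lowers the likelihood of harm but does not remove the point. The main-analysis sentence says that a term is added to a model. This one states what the independent variables will be, and the decision rule rests wholly on one of them.

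A reader might infer that a uniformly effective intervention is bound to be reported as modified by almost every characteristic. The document does not support that. It needs the model fitted exactly as listed, uncentred characteristics and an effect near 7.6 minutes, and no coding is stated.

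Three further criticisms are tempting and should not be attached.

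- Standard errors too small with 31 practices: the article does not say whether a small-sample correction is used, and with the arm term the rates above are close to 5%.
- GEE and missing outcomes: this is a choice of method, and no missingness mechanism is stated for this analysis.
- A required multiplicity correction: seven independent tests at 0.05 give 1 − 0.95⁷ = 30% for at least one false positive, but the characteristics are pre-specified and the article repeatedly describes this aim as exploration.

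**Conclusion.** The point holds in conditional form. The listed terms omit the study-arm main effect, and the random intercept contradicts the stated GEE. Nothing else in the article repairs either. Fitted as listed with uncentred characteristics, the product term mainly carries the overall effect: about 65–85% false positives per characteristic at the planned 7.6 minutes, about 23–35% at half of it, and about 4–8% with no arm effect, with centring or with the arm term. The exact percentages rest on assumed modifier means and SDs. The direction does not, because it follows from the formula for any characteristic whose mean is far from zero relative to its SD. The fault is confined to a secondary objective; the primary estimate and the sample size stand.

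**What to change.** Rewrite the model sentence so that each model contains study arm, the characteristic (centred if continuous), their product, and the time terms needed to target the 6-month effect. State that modification is judged only on the arm-by-characteristic term at 6 months.

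Then resolve the method in one of two ways: fit the model within the linear mixed model of the section Effectiveness of the activate intervention, keeping its random intercepts; or keep GEE and delete the random intercept. The test for baseline minutes needs a line of its own, since that variable cannot serve both as modifier and as a repeated outcome in the same model.

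Reporting the seven interactions as exploratory, with estimates and 95% CIs, is optional.

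The cost is a few sentences. Data and design do not change, and the article reports that the trial was still collecting data, so the correction can be made before analysis.

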#### Secondary outcomes

The following are secondary outcomes of this trial:Sedentary behaviour using the accelerometer to measure the number of minutes in the sedentary category (<1.8 METs)Self-efficacy for physical activity using the Exercise Self-efficacy Scale [47–49]Patient activation using the PAM-13 short form [50, 51]Health status using the EQ-5D questionnaire [52]

Potential effect modifiers to investigate which patient characteristics modify change in physical activity level include age, depression measured using the Hospital Anxiety and Depression Scale [53, 54], body mass index (BMI), level of education, social support using the Multidimensional Scale of Perceived Social Support [55], patient-provider relationship using the Communication Assessment Tool [56], and baseline number of minutes of moderate to vigorous level of physical activity using the accelerometer.

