## Discussion

Despite the growing evidence for their effectiveness, so far self-management interventions show small effects on health outcomes. The effectiveness of interventions is ambiguous, and the question who benefits most from these interventions is still unanswered. With the Activate study, we expect to shed light on the effectiveness of self-management interventions and explore which subgroup of patients benefits most. The effectiveness of this intervention and understanding which patients benefit from the intervention may lead to a broader application of this intervention in supporting patients to enhance behaviour change in other self-management components (e.g., dietary intake, alcohol use, medication adherence and smoking cessation).

The Activate intervention was comprehensively developed using the BCW and was applied to the behaviour of both patients and nurses. Because the role of a competent health care provider is essential in the delivery and fidelity of self-management interventions [33, 34, 62, 63], we aimed to equip nurses with training that supports them to increase their skills and competencies to adequately deliver the intervention.

This study has several strengths. We performed a detailed analysis of the behaviour of both patients and nurses. Subsequently, BCTs were selected and described, which will enhance reproducibility of the intervention. Furthermore, this cluster RCT is being conducted across several general practices in different urbanisation areas in the Netherlands with the patient’ s own primary care nurse, rather than trained researchers, delivering the intervention. This strengthens the generalisability and relevance of the findings from this trial for primary care. Another methodological strength is the use of the informed consent for postponed information procedure, which reduces selection bias by attrition or dropout of patients. In our study, the control group might be dissatisfied at not receiving the intervention, which would increase the risk of biased results. Changes in outcome may be affected only because of a demoralized and perhaps less motivated control group.

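### Seven effect modifiers are each judged at p<0.05 with no control across the seven and no exploratory caveat beside the rule

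*Protocol article*

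**What the plan says.** The Potential effect modifiers part of the Statistical analysis section states that "pre-specified patient characteristics are selected" and lists them: "age, BMI, level of education, social support, depression, patient-provider relationship and baseline number of minutes of physical activity". The Secondary outcomes section gives the same seven, in a sentence that opens "Potential effect modifiers to investigate which patient characteristics modify change in physical activity level include age, depression".

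Each characteristic has its own model: "we will use GEEs for each of these patient characteristics separately". The decision rule follows: "Effect modification will be considered significant if the interaction term shows a level of significance <0.05".

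The article gives no adjustment across the seven tests and no global interaction test. That section also carries no statement that a significant interaction only generates a hypothesis.

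The article does not describe the status of these analyses in one way. The list of objectives at the end of the Background makes them one of three secondary objectives and uses the verb *identify*. The Abstract and two other places in the Background speak of exploring who benefits, and the Discussion section says the trial will "explore which subgroup of patients benefits most".

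**The concern.** A rule that declares a modifier significant at 0.05, applied seven times, controls the error of each test but not of the set. The natural report is a list of which characteristics passed. A reader of that list needs to know how often at least one would pass by chance alone.

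At stake is a statement that some type of patient benefits more or less, made under a published significance rule, when the finding is chance. The Abstract links knowing what works and for whom to further implementation, so such a statement could be taken up.

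The rule is printed in the article, so this is not a detail left to an analysis plan that is not shown. An adjustment in such a plan would still leave the printed rule to be corrected.

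**Working it through.** **Inputs from the article**
- Number of tests: 7, one model each (Potential effect modifiers; same list in Secondary outcomes).
- Level per test: 0.05, unadjusted (Potential effect modifiers).
- Mean 38 minutes, SD 18.1, difference of 20%, intra-cluster correlation 0.05, 279 patients, 15% dropout (Sample size calculation).

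**The plan's own figure.** The article states no error rate for the set of seven tests, so there is none to reproduce. The sample size inputs, used only for the power illustration below, do reproduce:
- Difference = 0.20 × 38 = 7.6 minutes.
- n per arm = 2 × [18.1 × (1.960 + 0.842) / 7.6]² = 89.04.

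This agrees with "Taking a power of 80% and a significance level of 5% into account requires 89 patients per arm", taking the 5% as two-sided.

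**Chance of at least one false modifier, none of the seven being real**
- Independent tests: 1 - 0.95^7 = 1 - 0.698 = 0.302, or 30%.
- Expected number of false modifiers: 7 × 0.05 = 0.35, whatever the correlation.
- Upper bound under any dependence: 7 × 0.05 = 35%.

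The documents give no correlations among the modifiers. I therefore assumed a range and simulated seven equally correlated two-sided z-tests, with 1,000,000 draws per value:

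| Correlation between test statistics | At least one false modifier |
|---|---|
| 0 | 30% |
| 0.1 | 29.7% |
| 0.2 | 28.7% |
| 0.3 | 27.2% |
| 0.5 | 22.9% |

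**What formal control would cost in power.** Assume a binary modifier that varies between patients within a practice, and an interaction of 7.6 minutes, as large as the whole planned treatment effect.
- Patients with data: 279 × 0.85 = 237.
- The modifier contrast is made within practices, so the relevant SD is 18.1 × √(1 - 0.05) = 17.64.
- SE of the interaction for a 50/50 modifier = 4 × 17.64 / √237 = 4.58 minutes, and 7.6 / 4.58 = 1.66.
- Power at 0.05: Φ(1.66 - 1.96) = 38%.
- Power at the strictest Holm step, 0.05/7 = 0.0071 (critical value 2.69): Φ(1.66 - 2.69) = 15%.
- For a 30/70 modifier, SE = 2 × 17.64 / √(237 × 0.3 × 0.7) = 5.00 and 7.6 / 5.00 = 1.52. Power is Φ(1.52 - 1.96) = 33% at 0.05 and Φ(1.52 - 2.69) = 12% at the strictest step.

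**The case against.** The strongest defence is that these are few, pre-specified secondary analyses that use proper interaction terms, and that statisticians differ on whether such analyses need control across the set. The article also speaks of exploration in several places. Much of this stands: it is why formal adjustment is not required and why the point is modest. It does not remove the point. Pre-specification prevents picking modifiers after seeing the data, but it leaves the error over seven tests unchanged. If exploration is the intent, a bare significance threshold is the wrong rule to print for it.

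A second objection is that 30% depends on all seven being null and independent. That is correct. The Background cites earlier, inconclusive evidence for some related characteristics, such as age, depressive symptoms and education, so the case in which none is real need not hold.

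Three stronger readings are tempting, and the documents do not support them.
- A reader might infer that a large share of significant modifiers would be false. That share depends on how many are real, which the documents do not give. At 38% power and a 5% level the expected share is 0.30/0.68 = 44% if one of seven is real, 0.25/1.01 = 25% if two are, and 0.20/1.34 = 15% if three are.
- A reader might infer that the planned GEE pushes the error well above 30%. The article does not fix the working correlation, the clustering level or the variance estimator, so no figure can be attached to the plan. That would also be a matter of model validity, which a multiplicity adjustment does not cure.
- A reader might infer that this question is the trial's principal contribution. Effectiveness is the primary objective; effect modification is one of three secondary ones.

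**Conclusion.** The concern holds in a limited form. The article prints a per-test significance rule for seven modifiers, with neither control across them nor a caveat beside the rule, and its wording wavers between exploring and identifying. If none of the seven is real, the chance of at least one false modifier is about 30% under independence and 23% to 30% for correlations from 0.5 down to 0. The correlations are assumed. The power figures are illustrative: they rest on a binary modifier, 237 patients and a 7.6-minute interaction, whereas several of the seven are naturally continuous and the article plans no dichotomy. The primary comparison of the arms is not touched. This is a cheap improvement to what the trial may claim, and no threat to its main result.

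**What to change.** In Potential effect modifiers, replace the significance rule with a statement that all seven interaction analyses are exploratory and hypothesis-generating, and that every interaction estimate will be reported with its 95% CI whatever its p-value. In the list of objectives, change the verb *identify* to match the exploratory wording used elsewhere in the article.

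The cost is a few words and the loss of any confirmatory claim about a single modifier. The Trial status section puts the trial in data collection, so by that account the wording can be settled before analysis.

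If the sponsor does want a confirmatory claim, Holm across the seven p-values is an option. Under the assumptions shown, it could lower power for one interaction from about 38% to about 15% at its strictest step, which is a poor trade for a question the article mostly calls exploratory.

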#### Process evaluation

Quantitative data will be analysed using descriptive statistics. The audio recordings will be transcribed and independently analysed by two researchers using the coding list developed for this study. The interviews with nurses and patients to explore their experiences with the intervention will be audiotaped and transcribed. These transcriptions will be analysed and qualitatively described using thematic analysis as described by Braun and Clarke [60].

#### Sample size calculation

The present trial is powered to detect a mean difference between the intervention arm and control arm of 20% in number of minutes of at least a moderate level of physical activity. Based on the results of the It’s LiFe! trial [61], the mean level of physical activity in participants is 38 minutes (SD 18.1). The It’s LiFe! trial is a three-arm trial performed in primary care in the Netherlands with patients with chronic obstructive pulmonary disease and DM2 in which the researchers aimed to increase physical activity with a self-management support programme and the It’s LiFe! tool (a monitoring and feedback tool). This study revealed an increase in physical activity of 27%, but only in the counselling and It’s LiFe! tool group, objectively measured with the Pam AM300. We consider an increase in physical activity of 20% as reasonable to achieve. Taking a power of 80% and a significance level of 5% into account requires 89 patients per arm. Assuming an intra-cluster correlation of 0.05 and a cluster size of 8 patients per general practice requires 30 or 31 participating practices [59]. Allowing a patient dropout rate of 15%, we aim to recruit 279 patients in total and 9 or 10 patients per general practice.

#### Stopping rules

There are no formal stopping rules. If a patient decides to withdraw, the nurse will stop the intervention for that patient. Patients can withdraw from the study at any time.

